### 5.2. Sample Size

The sample size for each arm was calculated using the statistical power of G Power [46]. The parameters applied included (a) an alpha level of 0.05 and (b) a statistical power of >80%. The effect size (ES) is estimated based on previous studies [47]. At least 30 subjects in each group were sufficient. Considering a 20% dropout rate, 36 participants in each group were recruited for the trial, therefore there were 72 participants at baseline.

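### The 20% dropout allowance is miscalculated: 36 per group leaves about 28 to 29 completers, below the plan's own minimum of 30

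*Protocol article*

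**What the plan says.** The sample-size argument is in the Protocol article, section 5.2 (Sample Size). It gives "an alpha level of 0.05" and "a statistical power of >80" per cent as the parameters. For the effect it says only "The effect size (ES) is estimated based on previous studies", with no number. It concludes "At least 30 subjects in each group were sufficient", then makes the dropout allowance and arrives at its target: "Considering a 20% dropout rate, 36 participants in each group were recruited for the trial", and "therefore there were 72 participants at baseline". The abstract repeats the total of 72. No other section gives a different dropout rate, required size or inflation rule.

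**The concern.** The required size, the dropout rate and the enrolled size are all stated, and the third does not follow from the first two. The purpose of the allowance is that the required 30 per group remain after the expected loss. Adding 20% to 30 does not achieve this, because dropout removes 20% of those enrolled, not 20% of those required.

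At stake are the dropout tolerance that the article claims for its 72 participants and, depending on how the figure of 30 was reached, the stated power at that dropout rate.

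**Working it through.** **Inputs, all from section 5.2:** required completers per group, 30; dropout, 20%; enrolled per group, 36; total, 72.

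**1. Reproducing the plan's figure.** 30 × (1 + 0.20) = 36 per group, and 2 × 36 = 72. Both match exactly, so the allowance appears to have been made by multiplication.

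**2. Completers at the stated dropout.** 36 × (1 − 0.20) = 28.8 per group, or 57.6 of 72. In whole people, losing 7 of 36 leaves 29 and losing 8 leaves 28. Both are below 30.

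**3. The allowance that matches 20%.** n / (1 − d) = 30 / 0.80 = 37.5, rounded up to 38 per group, 76 in total. Check: 38 × 0.80 = 30.4, which meets the minimum. The gap is 38 − 36 = 2 per group, 4 in total, or 4/72 = 5.6% of the planned total.

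**4. The dropout that 36 does cover.** 1 − 30/36 = 6/36 = 16.7%.

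**5. Power, as an illustration only.** Section 5.2 gives no effect size, sidedness or test, so these figures rest on assumptions: a two-sample t-test on completers, alpha 0.05, and an effect size d back-solved from an assumed power at 30 per group.

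| Assumption | Implied d | Power at 28 | at 29 | at 30 |
|---|---|---|---|---|
| Exactly 80% at 30, two-sided | 0.736 | 77.1% | 78.6% | 80.0% |
| Exactly 80% at 30, one-sided | 0.650 | 77.5% | 78.8% | 80.0% |
| Exactly 80% at 29, two-sided | 0.749 | 78.6% | 80.0% | 81.4% |
| Exactly 80% at 28, two-sided | 0.762 | 80.0% | 81.4% | 82.7% |

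In the two-sided test, 30 is the smallest size with at least 80% power when d runs from 0.736 up to just under 0.749. Over that range, power is about 77.1% to 78.6% at 28 per group, and from 78.6% to just under 80% at 29. The last row applies only if 30 was rounded up from a smaller minimum.

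**The case against.** **Power.** A reader might infer that the trial definitely misses its stated power. The documents do not support that. Section 5.2 says that at least 30 per group were sufficient for power above 80%. It does not say that 30 gives exactly 80%, or that no smaller number would do. If 30 was rounded up from 28, power at 28 is still 80% and nothing is lost. This objection stands: the power consequence is conditional, and no power figure of ours belongs in the protocol text.

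**Analysis set.** Section 5.1 plans a GEE over three time points, with the last or baseline observation carried forward for missing data. A participant who drops out after baseline therefore stays in the analysis, and a completers-only t-test is only a stand-in for that analysis. This also stands as a limit on the power illustration. It does not repair the allowance: section 5.2 makes an explicit addition for dropout, and a value carried forward is not a new observation at either follow-up.

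**Size and timing.** The gap is 2 per group. Section 5.2 describes recruitment in the past tense, and section 4.2.1 schedules the programme for July to September 2023, before publication in December 2023. The figure of 38 may therefore matter only for reporting. That lowers the severity, but it does not make 36 less 20% equal to 30.

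**Conclusion.** The allowance is wrong as written. This rests only on figures in section 5.2 and needs no assumption about the effect: 36 per group covers 16.7% dropout, not 20%, and at 20% about 28 to 29 per group complete against a stated minimum of 30.

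Whether the stated power is also missed depends on whether 30 is the true minimum. If it is, power above 80% is not reached at the assumed dropout rate. Under the t-test illustration the loss is about 1.4 to 2.9 percentage points (80.0 − 78.6 and 80.0 − 77.1) when 30 gives exactly 80%, and power at 29 is close to 80% when power at 30 is slightly higher. The actual loss cannot be computed from the document.

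Severity is minor. The shortfall is small, and no outcome, test or decision rule changes.

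**What to change.** Keep the 72 participants and correct the dropout sentence in section 5.2 to say, in substance: *36 per group retains 30 per group at up to 16.7% dropout; at 20% dropout about 28 to 29 per group remain.* Add the power at 28 to 29 per group, recomputed by the sponsor from its own effect size, sidedness and test, and not taken from the illustration here. If 20% is kept as the planning rate, the matching target is 38 per group, 76 in total.

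The first option costs one sentence and one recalculation, and the stated dropout tolerance becomes slightly less favourable. The second adds 4 participants if recruitment is still open. If it has closed, 38 can serve only as the corrected planning figure in the report.

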### 5.3. Data Management

To truly protect the identity of the research participants and prevent a chain reaction caused by relevant personal information, this study will anonymize all the collected information and promise to keep it confidential. All information that may identify the participants will be used either anonymized or using a codename replacement. The questionnaire data will also be properly kept. Data will be destroyed 5 years after publication.

## 6. Discussion

This quasi-experimental study examined the effects of the FPCMP-Old Age Program intervention on frailty, physical activity, and nutrition in two groups of older adults (experimental and control). In the current study, many exercise programs were used in the community, including Vivifrail [16], Tai Chi [48], resistance exercises [49], and TRX [21]. These interventions based on exercise interventions should be highly recommended in treatment and prevention to improve physical function, functional capacity, and quality of life in frail older adults.

Many TRX studies had been conducted in adolescent athletes for performance enhancement [24,50], weight management [51], and as a cardiovascular and resistance training exercise [52]. The above-mentioned studies have shown that TRX exercises can train and improve strength, endurance, coordination, flexibility, and explosive power; reduce body fat, systolic and diastolic blood pressure, and waist circumference; and increase muscle mass [50,51,52]. However, some researchers reported that TRX training had no effect on cardiorespiratory endurance capacity [50].

Some of these studies developed short-term practical applications and small samples. Few experimental studies have been conducted on using TRX exercises to prevent frailty in older adults, and empirical results are lacking [21,26,50,51,52]. Considering whether the older adults have enough physical strength to perform TRX exercises safely, this study attempts to design a multiple-intervention program to integrate TRX exercises and nutritional intervention into the FPCMP-Old Age Program. We expect to develop interventions appropriate for the community domain to benefit long-term care and sustainable community development.

An additional advantage of this community-based intervention is that it will be conducted in a natural setting, allowing respondents to integrate changes into their daily lives in a real-life context. The intervention being examined is readily transferable to several professional groups in health care such as nurses, dietitians, and physiotherapists.

This study has several limitations. First, quasi-experimental studies’ lack of randomization may lead to selection bias. The main consideration is that communities willing to participate must obtain the consent of all older adults to participate in the program. In addition, the random sampling method is likely to cause dissatisfaction among the older adults in the community, because most older adults hope to participate in this project together. The sample was not randomized for pragmatic and ethical reasons, as it might be considered unethical not to prescribe exercise to frail older adults [53]. However, the lack of randomization resulted in the results being contaminated with confounding variables. Second, a potential limitation of this study is that participants and research nurses could not be blinded, as it would be impossible to blind them in non-drug trials. Therefore, performance bias may be unavoidable. In addition, to obtain the consent of all participants in the experimental group, participants must be informed of the risks of participating in the study. In this case, the “Hawthorne effect” may occur in the experimental group.

### FPCMP-Old Age Program Development Challenges and Solutions

Older adults should exercise cautiously, as their age and potential health conditions, such as heart disease, high or low blood pressure, diabetes, and severe degeneration of bones and joints, require careful consideration, regardless of their physical health status [54]. Professional medical personnel first evaluated age, past medical history, the medicine used, and whether there were risk factors for coronary artery disease; they also asked whether the older adults had experienced discomfort symptoms and restrictions during exercise, and measured blood pressure, heart rate, and blood oxygen before the activity exercise [54]. Implementing the FPCMP-Old Age Program should avoid injuries in participants, according to Gaedtke and Morat (2015), who studied the application of TRX [21]. It is worth noting that older adults are prone to knee, waist, or hip injuries owing to incorrect posture [21]. According to the recommendations, before each training session, the coach checked safety points to avoid injuries. The training time for older adults should be 30–45 min to ensure adequate training and physical recovery [55]. The ratio of the number of older individuals guided by trained coaches was 1:5 [21].

However, this intervention plan will face some practical challenges and limitations when planning to promote TRX exercises to the community, such as athletic trainers needing to receive TRX exercise training, health indicators of older adults (e.g., severe osteoporosis must be excluded), establishing safety standards, and a safe environment created (use floor mats or knee pads) to ensure the safety of the participants.

## 7. Expected Results and Possible Benefits

Exercise and adequate nutritional support appear to have promising effects on preventing frailty and improving physical activity and overall functioning, with significant effects on physical function and preventing frailty in older adults.Provide an exercise prescription-FPCMP-Old Age Program to prevent frailty in older adults and verify its effectiveness through the intervention of this study.

## 8. Conclusions

This trial will provide vital information to guide interventions to improve outcomes (frailty, physical activity, and nutrition) and inform the integration of nutrition and TRX exercises in community-dwelling older adults. Based on the evidence, we are convinced that this intervention program will be able to prevent frailty and the adverse effects associated with it in older adults.

## Figures and Tables

**Figure 1 healthcare-11-03188-f001:**
[figure not shown]
Overview of the flow of participants through the FPCMP-Old Age Trial. Adapted from the CONSORT diagram.

**Figure 2 healthcare-11-03188-f002:**
[figure not shown]
Total Resistance Exercises (TRX) program with FITT-VP.

**Figure 3 healthcare-11-03188-f003:**
[figure not shown]
Total Resistance Exercises (TRX) program protocol.

**Table 1 healthcare-11-03188-t001:** Primary and secondary outcomes for the participants of the study.

Outcome/Variable	Scale	Baseline (T0)	Immediately Post Intervention (T1)	3 Months Post Intervention (T2)
Descriptive variables	Demographic variables and Chronic Disease and Health Problems Scale	X		
Frailty	Tilburg frailty indicator (TFI-T)	X	X	X
Health function (1) Physical function	Senior Fitness Test (SFT)			
	Chair sit-and-reach test	X	X	X
	Back scratch test	X	X	X
	Chair stand test	X	X	X
	The Biceps Curl Test	X	X	X
	8-foot up-and-go test	X	X	X
	2 min step test	X	X	X
(2) Nutrition	Mini Nutritional Assessment-Short Form (MNA-SF)	X	X	X

X check on visit.
